Access to treatment is an enormous challenge, with only 10.7% of OUD patients who needed treatment in 2012 receiving it [11]. Effective treatment is complex and demanding because OUDs are chronic diseases that require ongoing medication, behavioral counseling, and overdose protection, as well as screening and treatment for infectious disease and comorbid psychiatric disease [2]. Effective treatment is also complex because affected populations differ in the etiology and course of their addiction, motivation for treatment, and reasons for relapse, including notable differences between men and women [12]. For example, women tend to progress more quickly from the start of substance use to the start of dependence, have a higher rate of cooccurring mood and anxiety disorders, and have better outcomes on buprenorphine than on methadone [12]. Finally, retention in treatment, which is known to reduce drug use [13], remains a challenge in treating OUDs [14–19]—so much so that treatment retention is often itself regarded as a desired outcome [20].

Testing and links to care for HIV and HCV are essential for people who inject opioids. Those who inject drugs are at greater risk of contracting HIV and are less successfully linked to [21–23] and retained in [24–26] clinical care. Antiretroviral therapy is recommended for all patients living with HIV, but treatment is under-used [27] and often suboptimally effective [23, 28] among people who inject drugs. HCV occurs primarily in people who inject drugs, with 90% of older injection-drug users infected [29–31]. HCV is the most common blood-borne infection in the US [32] and the most common cause of end-stage liver disease and the need for liver transplants.

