## Methods/design

### Study design, hypotheses, and outcomes

The study, a RCT, will assign 440 opioid users from three addiction treatment centers to receive either MAT + A-CHESS or MAT alone. Patients will be followed for 24 months. The primary hypothesis is that participants assigned to MAT + A-CHESS will have, compared with a control group, a lower percentage of days using illicit opioids. Secondary hypotheses are that those assigned to MAT + A-CHESS will have, compared to the control group, less use of other nonprescribed substances, higher quality of life, greater retention in treatment, and lower health service use. Secondary hypotheses related to HIV/HCV are that those assigned to MAT + A-CHESS will have higher screening and testing rates, greater medication adherence, fewer risk behaviors, and better linkage to care (i.e., referrals that result in in-person visits with providers). We also hypothesize that autonomy (or intrinsic motivation), competence, and relatedness [35] will mediate the effect of MAT + A-CHESS, along with negative affect and self-stigma. We will also determine the person-level factors that moderate the impact of MAT + A-CHESS versus MAT alone (e.g., gender, SUD severity, pain severity, severity of withdrawal symptoms, and loneliness). For patients receiving MAT + A-CHESS, we will examine whether patterns of using A-CHESS and communication style within peer discussion forums are predictors of study outcomes [36]. Figure 1 shows the logic and outcomes for the project. We will use quantitative and qualitative analyses to examine long-term impact, with survey data collected every 4 months during the 24-month period.

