### Interventions

#### Control condition: MAT

Patients in the control condition will receive treatment as usual including MAT. Treatment could consist of a recovery plan, medication, and regularly scheduled behavioral interventions such as monthly group counseling sessions, sessions with a substance abuse counselor, and Narcotics Anonymous/Alcoholics Anonymous (NA/AA) meetings. Medication may include methadone, injectable naltrexone, or buprenorphine. The sequence and duration of medication and behavioral interventions will vary by patient and site. Discussions with sites revealed that we should not try to control variations because they are tailored to individual patients. We will document which medications are used and will include as covariates when and how medications change between the 4-month surveys.

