### Randomization

The project director will use a computer-generated allocation sequence to randomize participants in a 1:1 ratio to MAT + A-CHESS or MAT alone, stratifying on gender and site and balancing on age, level of care (intensive outpatient treatment, day treatment, or weekly or monthly counseling), and whether patients had prior SUD treatment. The project director will inform the site coordinator of the group assignment by email; in the email, the participant will be identified only by study ID (the code used to make the identity of participants unknown). The site coordinator will initiate patients into the study condition and, if the patient is assigned to MAT + A-CHESS, provide training.

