At months 4, 8, 12, 16, 20, and 24. During phone surveys after baseline data collection, patients will complete a 120-day TLFB [54] to document their illicit opioid and other nonprescribed drug and alcohol use as well as health service use during the past 4 months. Health service use will be collected for the categories listed under “Health service use and cost” below. Patients will also complete measures of: relapse risk (Brief Addiction Monitor [55], nine items); pain severity (NRS scale [56], one item); HIV/HCV screening and link-to-care status (testing status and if tested, result, and if positive, whether the patient saw a medical provider); risk behaviors (HRBS [57], five items); status of current housing (two items) and employment (three items on type of employment, hours worked); quality of life (The Satisfaction with Life Scale [58], eight items); rating scale for withdrawal (three items); self-reported medication adherence (Morisky Medication Adherence Scale: MMAS-4 [59], four items); and loneliness (three items). We will collect number of phones lost, stolen, or broken (research records). For retention in treatment, we will take the proportion of appointments attended from clinic records. We will also determine if participants are engaging in other forms of treatment outside of the treatment facility, such as seeing a therapist, working with a sponsor, or attending NA/AA meetings.

Mediators. Self-determination theory (SDT) constructs will be assessed as follows: autonomy, Treatment Self-Regulation Questionnaire [60] (six items); competence, revised Drug-Taking Confidence Questionnaire [61] (eight items); and relatedness, our own bonding scale (five items). Negative affect will be assessed by Positive and Negative Affect: PANAS [62, 63] (20 items), and self-stigma by the self-devaluation subscale of the self-stigma in substance abuse scale [64] (seven items).

Moderators: we will focus our evaluation on gender but also collect data on other potential moderators (SUD severity as determined by the treatment site at intake using DSM-V criteria, pain as determined by the NRS-11, withdrawal, and loneliness).

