### Data analysis

#### Power and sample size justification

Primary analysis. Our study will be powered to detect a difference between MAT + A-CHESS and MAT in percentage of days using illicit opioids across the 24-month intervention period. Based on data from the two sites from which most study participants will be recruited, we assume 35% attrition over the course of the study, providing an *N* of 286. Using the power program by Hedeker et al. [69] and assuming up to cubic trends in the data, given expected attrition, recruitment of 440 patients will provide 80% power to uncover a standardized difference of .35 across the 24 months. From prior data [70, 71], this would be a difference of approximately three opioid use days/month depending on the observed standard deviation.

Secondary analyses. Power for examining intervention effects for the secondary outcomes would be similar as for the percentage of opioid use days, though the difference implied by the standardized difference of .35 will depend on the actual standard deviation of each measure. For secondary outcomes related to HIV and HCV, the sample size also provides 80% power to find a two-tailed difference in proportion screened for HIV/HCV of 16% [72] (conservatively assuming that screening for one group nears 50%, the point requiring the largest difference to achieve a specified power).

Mediation and moderation analyses. Power for detecting specific parameter changes in the structural model will be estimated using a procedure proposed by Satorra and Saris [73] that approximates the noncentral chi-square distribution. A total *N* of approximately 220 patients would provide adequate power (>.80) to detect a group difference in a parameter by 0.4 standard deviations (a moderate effect). Since our primary analysis projects a final *N* of 286, we are confident our secondary process analysis will have adequate power.

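### The secondary outcome of retention in treatment is measured by attendance at appointments, which does not measure whether patients stay in treatment

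*Protocol article*

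**What the plan says.** Retention is a named secondary outcome with a directional hypothesis: under Study design, hypotheses, and outcomes, the MAT + A-CHESS arm is expected to show "higher quality of life, greater retention in treatment, and lower health service use". The Background makes the concept clear. It describes keeping patients in treatment as a persistent difficulty, "so much so that treatment retention is often itself regarded as a desired outcome".

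The only operational definition is under Measures, in the paragraph on the 4-monthly assessments: "For retention in treatment, we will take the proportion of appointments attended from clinic records". The article does not say which appointments form the denominator, how the time after a patient leaves is counted, or what value is given to a period with no appointments. The same paragraph says that treatment outside the facility will be recorded, but does not make it part of the retention measure.

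No common visit schedule is given. Under Control condition: MAT, "The sequence and duration of medication and behavioral interventions will vary by patient and site", and the team chooses not to control that variation. Under Randomization, patients differ in "level of care (intensive outpatient treatment, day treatment, or weekly or monthly counseling"). Follow-up is the same for everyone: "Patients will be followed for 24 months".

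**The concern.** Retention asks whether, and for how long, a patient stays in treatment. The proportion of appointments attended asks how reliably a patient turns up. The two separate at the event of interest, which is leaving treatment. If the denominator counts only booked appointments, it stops growing when the patient leaves, and the departure itself costs nothing in the score.

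The Abstract plans mixed-effects models for the secondary outcomes at six time points. If the proportion is computed per 4-month period, a patient who has left and has nothing booked gives 0/0 for every later period. The value would then be undefined because the patient was not retained.

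At stake is whether the trial can answer its retention hypothesis. Two arms could differ clearly in the share of patients still in treatment while this measure shows little difference, or one in the opposite direction.

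**Working it through.** The article states no figure for this outcome, so there is none to reproduce. The calculations below are illustrations. The 24-month follow-up comes from the article; visit counts, leaving times and attendance rates are assumptions.

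**1. Single patients, appointments booked as denominator.**
- Patient A attends 4 of 4 visits and leaves in month 1: 4/4 = 100%.
- Patient B stays 24 months and attends 40 of 48 visits: 40/48 = 83.3%.
- On months in treatment out of 24: A scores 1/24 = 4.2%. B scores 24/24 = 100%, provided the 8 missed visits leave at least one attended visit in each month.

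The two measures rank the patients in opposite order.

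**2. Effect of the denominator for a patient who attends everything until leaving.** Assume weekly visits (104 over 24 months) or monthly visits (24).

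| Leaves at | Booked denominator | Full 24-month denominator |
|---|---|---|
| Month 3 | 13/13 or 3/3 = 100% | 13/104 or 3/24 = 12.5% |
| Month 6 | 100% | 26/104 or 6/24 = 25% |
| Month 12 | 100% | 52/104 or 12/24 = 50% |

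The unstated denominator decides whether such a leaver scores 100% or something near the time actually spent in care.

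**3. Group mean.** Let p be the fraction who leave at month 4, L the attendance rate of leavers while in care, and S the attendance rate of stayers.
- Booked denominator: mean = pL + (1 − p)S = S + p(L − S).
- Fixed 24-month denominator: mean = pL(4/24) + (1 − p)S.
- Still in treatment at 24 months: 1 − p.

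With S = 80% and three values of L:

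| L | Booked, p = 20% | Booked, p = 50% | Fixed, p = 20% | Fixed, p = 50% |
|---|---|---|---|---|
| 95% | 83.0% | 87.5% | 67.2% | 47.9% |
| 80% | 80.0% | 80.0% | 66.7% | 46.7% |
| 60% | 76.0% | 70.0% | 66.0% | 45.0% |

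For example, in the first row: 0.20 × 95 + 0.80 × 80 = 83.0 and 0.50 × 95 + 0.50 × 80 = 87.5.

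In every row, retention at 24 months falls from 80% to 50%, a loss of 30 points. The booked score changes by 30 × (L − S): it rises 4.5 points when leavers had attended better than stayers, does not move when they had attended equally, and falls 6 points when they had attended worse by 20 points. The fixed-denominator mean falls by 19 to 21 points throughout.

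So on the booked denominator the sign is set by L − S. Even when the sign is right, the change is small unless leavers had attended very much worse than stayers.

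**The case against.** The strongest reply is that the denominator in this reading is supplied by the reader. The article does not say attended over booked. A denominator covering all visits planned over 24 months would count absence after leaving, and a condensed article may leave that detail to a fuller document. This stands in part: it cannot be said that the plan will score early leavers as fully retained, only that it can. But the article describes schedules that vary by patient and site and in frequency, so it offers no common planned count. Moreover, the measure it does state is attendance, so the difficulty is the choice of measure and not only a missing detail.

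Some stronger readings are tempting and are not supported:
- **That the measure is biased against A-CHESS.** A reader might infer that marginal patients kept in care by the app would miss visits and pull its score down. That needs an assumption about their attendance, and the article has no such data. The third row of the group table shows a case with no reversal.
- **That undefined periods will drop out of the mixed model.** The article does not say how they are handled; they could be scored as zero. Its pattern-mixture and worst-case analyses are planned for the longitudinal analysis generally. The reasoning and example given there concern patients' survey responses, and an undefined clinic-record ratio is not mentioned.
- **That differing visit frequency by site or level of care biases the comparison.** A proportion already scales for frequency, and randomisation is stratified on site and balanced on level of care. The variation matters here only because it leaves no common denominator.
- **That discharge dates are already being extracted.** The article mentions only appointment attendance from clinic records.

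It is also fair that counting every month after leaving as failure would misclassify patients who complete treatment as planned or move to another provider. Any replacement needs a rule for them.

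**Conclusion.** The point holds as a badly chosen measure for one secondary outcome. Attendance at appointments does not measure persistence in treatment, and the article gives no rule that would make it do so.

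If the denominator is booked appointments, an early leaver with perfect attendance scores 100%, above a 24-month patient who misses some visits. Under the illustrative inputs, a 30-point loss of true retention moves the group score by anything from +4.5 to −6 points. That range depends on leavers exiting at month 4, stayers attending 80% and leavers attending 60% to 95%. The mechanism does not depend on these values, but the size and direction do, and nothing in the article fixes them.

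The primary outcome, days of illicit opioid use, is unaffected, as is its power calculation. The change is worth making so that the retention hypothesis can be tested; it is not a condition for the validity of the trial's main result.

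**What to change.** Define retention from clinic visit records over a period fixed at randomisation. Either of these would serve:
- months with at least one recorded treatment visit, out of 24; or
- time from randomisation to the last attended treatment visit, up to 24 months.

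Time after leaving counts as not retained, so every randomised patient has a defined value. State in advance how planned completion and transfer to another provider count, using the outside-treatment information already collected at the 4-monthly surveys. The months measure still takes in some attendance for patients on monthly visits, since one missed visit loses a month; time to last attended visit avoids this.

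Keep the proportion of appointments attended, state its denominator, and report it separately as adherence while in care.

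The cost is a little more record extraction (dates of attended visits, not only a ratio) and one added classification rule. Neither the randomisation nor the survey schedule changes. The article reports 23 of 440 participants recruited on 8 June 2016, so at that stage the definition could be changed before most outcome data accrued.

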### Timeline

Recruitment began in April 2016 and will end in February 2018. The intervention period will end in February 2020. Figure 5 shows the study timeline.

**Fig. 5 Fig5:**
[figure not shown]
Study timeline

### Data analysis

#### Power and sample size justification

Primary analysis. Our study will be powered to detect a difference between MAT + A-CHESS and MAT in percentage of days using illicit opioids across the 24-month intervention period. Based on data from the two sites from which most study participants will be recruited, we assume 35% attrition over the course of the study, providing an *N* of 286. Using the power program by Hedeker et al. [69] and assuming up to cubic trends in the data, given expected attrition, recruitment of 440 patients will provide 80% power to uncover a standardized difference of .35 across the 24 months. From prior data [70, 71], this would be a difference of approximately three opioid use days/month depending on the observed standard deviation.

Secondary analyses. Power for examining intervention effects for the secondary outcomes would be similar as for the percentage of opioid use days, though the difference implied by the standardized difference of .35 will depend on the actual standard deviation of each measure. For secondary outcomes related to HIV and HCV, the sample size also provides 80% power to find a two-tailed difference in proportion screened for HIV/HCV of 16% [72] (conservatively assuming that screening for one group nears 50%, the point requiring the largest difference to achieve a specified power).

Mediation and moderation analyses. Power for detecting specific parameter changes in the structural model will be estimated using a procedure proposed by Satorra and Saris [73] that approximates the noncentral chi-square distribution. A total *N* of approximately 220 patients would provide adequate power (>.80) to detect a group difference in a parameter by 0.4 standard deviations (a moderate effect). Since our primary analysis projects a final *N* of 286, we are confident our secondary process analysis will have adequate power.

Missing data. In previous addiction work, we completed 85% of surveys at 4, 8, and 12 months. We anticipate greater reductions at months 16, 20, and 24, reaching about 65% by month 24. In previous studies, we have kept missing data on core items in a survey to about 2% and expect a comparable rate in this study. In addiction treatment, data are not likely to be missing at random (i.e., the probability that data are missing is related to what the data would have been had the data been observed). For example, some patients may not want to disclose opioid use in surveys. Because this may lead to biased parameter estimates for our models, we will identify missing data patterns and use pattern-mixture modeling to test the sensitivity of our longitudinal intervention analysis to missing data assumptions [74–77] and conduct other sensitivity analyses after imputing missing data with a range of clinically plausible values based on explicit assumptions for the missing data (e.g., best-case, worst-case; with and without multiple imputation) [78–80].

Intention-to-treat and subject noncompliance. Standard intention-to-treat (ITT) estimates the average treatment effect by comparing outcomes based on assignment to treatment, but ignoring use of the treatment. Because ITT estimates do not represent treatment efficacy under noncompliance (e.g., a patient is randomized to A-CHESS but does not use the system), we will address noncompliance by also estimating treatment effects only for compliers using as-treated, per-protocol [81], and CACE (Complier Average Causal Effect) [82].

Dropout rates. In our A-CHESS RCT with alcohol-dependent patients [33], 88 patients were using opioids as well as alcohol; 261 were not using opioids. We compared the post-test survey response rate of opioid-using patients to the response rate of patients who did not use opioids. The non-opioid-using patients’ response rates were 94.3% at 4 months; 90.6% at 8 months, and 86.7% at 12 months. The opioid-using patients’ response rates were 91.2%, 86%, and 79.1%. Response rates declined in a relatively linear fashion in both groups, with reductions of about 5 percentage points in each period. We assumed a 65% response rate at 24 months by continuing the drop off rate for each of the three periods from 79% to 74% to 69% to 64%. Hence, we believe it is likely that by the end of the study we will still be able to reach 65% of patients originally enrolled.

Mediation analysis. Mediator variables will all be collected in the first two visits (at the 4- and 8-month visits) while the outcome (illicit drug use days) will be collected at months 12, 16, 20, and 24. Because mediator-outcome relations might reflect the effects of drug use while the mediator is being assessed (e.g., drug use might suppress ratings of competence), drug use that occurs during the mediator assessment period will be covaried out of models to examine and control its influence. Moreover, to assess the nonorthogonality of the mediators (which seems likely with the self-determination variables), we will use multiple mediator analyses based on a Bayesian approach illustrated in Yuan and MacKinnon [83]. This Bayesian estimation of the meditational models can be implemented through Markov Chain Monte Carlo (MCMC) techniques. Unlike more traditional estimation methods, such as maximum likelihood or least squares methods, for example, MCMC methods rely on sampling techniques to estimate model parameters and resulting mediation effects (i.e., iterative sampling from the parameter distributions is used to estimate confidence intervals to identify significant effects). An appealing feature of the method is its relative ease of implementation, particularly for complex statistical models. Similar to Yuan and MacKinnon, we will implement MCMC using WinBUGS 1.4 [84]. The multiple mediator models will be conducted with only those mediators shown to be significant in univariate models. See Bolt et al. [85] for our previous application of this analytic approach.

Qualitative analysis. Content analysis [86] of interview transcripts will describe the role that MAT + A-CHESS plays in sustaining opioid recovery and reducing HIV/HCV risk; identify potential improvements in MAT and A-CHESS; and supplement the quantitative analysis. UW research staff will: (1) construct a coding scheme [87] by combining categories flowing from the research questions, categories used in previous studies, and a preliminary examination of the data. Ideas will be our unit of analysis (rather than words or paragraphs) to capture references to a concept as well as direct statements about it, (2) test the coding scheme on a sample of data. Three coders will independently code the data in NVivo. We will calculate intercoder reliability and develop a set of coding instructions to insure reliability of at least .80, (3) code the full dataset and create a conceptual model to help explain the mechanisms by which, and conditions under which, the interventions affect opioid use and HIV/HCV screening. These conclusions will help us understand the benefits of and modifications needed for MAT + A-CHESS (and MAT alone) to sustain recovery over the long term.

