Triage and feedback functionality is designed to derail the relapse process, giving the patient just-in-time, tailored coping support. A-CHESS will be customized at the start by each patient to set options that will be triggered in a moment of need. For example, if a patient reports a craving triggered by environmental cues, such as seeing someone else use, A-CHESS might remind the patient of relaxation exercises, connect them to online peer support and the healthy events calendar, and/or notify a counselor, who may initiate contact via text or private message. Participants whose patterns of using A-CHESS demonstrate they are likely to stop using the system will receive automated messages and tailored messages from coaches to encourage them to reengage.

The counselor dashboard [43], developed by addiction physicians and psychologists, harvests clinically relevant data from A-CHESS and presents it to counselors to help them quickly: (1) identify patients who may be at high risk for relapse and/or benefit from clinical intervention, (2) see a detailed analysis of a patient’s recent history, e.g., trends in individual BAM items, A-CHESS use, and relapse data, and (3) intervene with patients (e.g., through texting in A-CHESS). When a counselor logs into the counselor dashboard, he sees ‘red pins’ generated when A-CHESS (using counselor-determined priorities) detects that a patient may be at high risk. The counselor can adjust the cutoffs for red pins so the ones he sees are most useful.

HIV/HCV services. A-CHESS will integrate components of our team’s existing computerized risk reduction systems that collect data on patients’ HIV/HCV risk behaviors and deliver behavior change interventions tailored to the patient’s self-reported readiness for change. At enrollment, participants in both study conditions will be asked if they have been screened for HIV and HCV. Patients who test negative or decline testing at baseline will be sent reminders from A-CHESS about future testing at a frequency based on reported risk behaviors. Patients found to be HIV or HCV-positive will be provided with targeted multimedia health education content, access to online resources, and location-specific links to clinical care and case management.

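### Linkage to care is recorded only for tested, positive patients, a group A-CHESS can change after randomisation, so the unqualified claim of power similar to the primary outcome does not hold for linkage among positives

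*Protocol article*

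**What the plan says.** The HIV/HCV secondary hypotheses under Study design, hypotheses, and outcomes are "higher screening and testing rates, greater medication adherence, fewer risk behaviors, and better linkage to care", with linkage explained there as referrals that lead to an in-person provider visit. In the follow-up surveys (Measures), linkage is captured through a chain of items: "testing status and if tested, result, and if positive, whether the patient saw a medical provider".

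The paragraph on HIV/HCV services in the description of the experimental condition states: "Patients who test negative or decline testing at baseline will be sent reminders from A-CHESS about future testing". Only the MAT + A-CHESS arm has that system.

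Under Power and sample size justification, "we assume 35% attrition over the course of the study", which leaves 286 of 440, and the planned recruitment "will provide 80% power to uncover a standardized difference of .35 across the 24 months". The paragraph on secondary analyses then adds: "Power for examining intervention effects for the secondary outcomes would be similar as for the percentage of opioid use days". The only HIV/HCV outcome given its own power figure is the proportion screened (80% power for a 16-point difference, with one group near 50%).

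HIV/HCV status is also collected in the baseline survey (Measures, Intake and baseline), which the Recruitment section places before randomisation.

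**The concern.** Two things follow from recording linkage along the chain tested, positive, seen.

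First, the patients with a linkage value are a subset of the 286. A power statement built on 286 does not carry over to that subset unless the subset is nearly everyone.

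Second, membership of the subset can depend on treatment. If the reminders work, some patients in the A-CHESS arm learn that they are positive who would not have been tested under MAT alone. If those extra patients are harder (or easier) to link, the linkage percentages among positives differ between arms even when A-CHESS has no effect on linkage for any given patient. The trial could then report a lower linkage percentage for the arm in which more people reached care.

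**Working it through.** **Inputs from the protocol article.** 440 randomised 1:1; 35% attrition; 80% power at .35 SD; screening near 50% in one group with a 16-point difference.

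**Assumed.** Two-sided alpha 0.05 (not stated; only the screening figure is called two-tailed). A share f of completers who are tested and positive (not given for this population), split equally between arms.

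**The plan's own figures.**
- Completers: 440 × 0.65 = 286, or 143 per arm.
- Primary, simple two-sample approximation: power = Φ(d√(n/2) − 1.96) = Φ(0.35 × √71.5 − 1.96) = Φ(1.00) = 84.1%. The stated 80% comes from a longitudinal power program whose correlation inputs are not given, so it cannot be reproduced exactly. The stated figure is the more cautious of the two.
- Screening, 50% v 66% with 143 per arm: 78.6%, close to the stated 80%.

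The full-sample figures are therefore credible for outcomes that every completer has.

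**Linkage among positives.** Replace n = 143 by 143f per arm. Detectable SD at 80% power = 2.80 × √(2/(143f)). The last column is the detectable difference between two proportions centred on 50%.

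| Share positive (assumed) | Total positives | Power at .35 SD | Detectable SD | Detectable points |
|---|---|---|---|---|
| 10% | 29 | 15% | 1.05 | 50 |
| 20% | 57 | 26% | 0.74 | 36 |
| 30% | 86 | 37% | 0.60 | 30 |
| 50% | 143 | 55% | 0.47 | 23 |
| 75% | 214 | 73% | 0.38 | 19 |
| 90% | 257 | 80% | 0.35 | 17 |

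Example at 30%: n = 42.9 per arm, 0.35 × √21.45 − 1.96 = −0.34, and Φ(−0.34) = 37%.

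**Selection, illustrated with assumed rates.** Let 50% be tested in either arm and a further 16% only because of A-CHESS (the protocol's screening difference). Let 30% of each group be positive. Usual testers link at 70% and extra testers at 40%, and A-CHESS does not change linkage for any individual who is tested.
- Among positives: control 70.0%; A-CHESS (0.50 × 0.70 + 0.16 × 0.40)/0.66 = 0.414/0.66 = 62.7%, a difference of −7.3 points.
- Over all patients in the arm: control 0.50 × 0.30 × 0.70 = 10.5%; A-CHESS 0.30 × 0.414 = 12.4%.

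The first comparison favours MAT alone, while the second shows more A-CHESS patients reaching care. If extra testers linked at the same rate as usual testers, the distortion would be zero.

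**The case against.** The strongest reply is that the survey wording describes an item sequence and does not fix an analysis denominator. No sentence says that linkage will be compared among positives only. The hypotheses are framed by assigned arm, an all-randomised version can be computed from the same items, and choosing a denominator is ordinary work for an analysis plan that is not shown. This stands in part: the positives-only denominator is implied by how linkage is measured and defined, not stated. It does not rescue the power sentence, which the protocol itself states without exception.

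A reader might infer three stronger claims that the protocol does not support.
- *That linkage exists only for patients found positive after randomisation.* Status is collected at baseline, before randomisation, so some positives are known by then, and comparing them by arm remains a randomised comparison.
- *That adherence has the same defect.* The abstract and the hypotheses list it under HIV/HCV, but the four-item adherence scale in Measures names no drug and no subset, and every participant enters on MAT medication. The text is ambiguous and does not establish the defect.
- *That power for linkage cannot be similar to the primary.* It could be if about 90% of completers were positive. The Background does cite 90% infected, but for older injection-drug users. Eligibility here requires neither older age nor injection, so that rate cannot simply be carried over, and it cannot be excluded by calculation either.

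It is also fair to say that the distortion in the illustration runs against A-CHESS, and that its size rests entirely on assumed rates.

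**Conclusion.** The point holds for linkage to care. As measured, linkage has a value only in tested, positive patients, and A-CHESS is designed to enlarge that group in one arm. A comparison among all known positives therefore conditions partly on a consequence of treatment. The statement of similar power is unsupported for that comparison: power at .35 SD is about 15% to 73% for 10% to 75% positive, and reaches 80% only near 90%. These figures rest on a simple two-sample approximation, equal numbers of positives per arm, two-sided alpha 0.05 and a share positive that the document does not supply. The selection mechanism follows from the text, but its direction and size do not.

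For adherence the conclusion is conditional on which medication the scale covers. Severity is low to moderate. One secondary outcome is clearly affected, and the primary outcome and the screening power figure are not.

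**What to change.** - Define linkage over all randomised patients: yes if tested, positive and seen by a provider by month 24, otherwise no. State how patients lost to follow-up are counted.
- Add a supporting comparison restricted to patients known positive at baseline.
- In the paragraph on secondary analyses, limit the similar-power sentence to outcomes measured in everyone. For linkage among positives, give the expected number positive with the resulting power range, or label the comparison exploratory.
- State which medication the adherence scale refers to. If it is HIV/HCV medication, apply the same restrictions.

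The cost is wording only, because the items are already collected. The stated power for linkage becomes less favourable. The all-randomised measure combines testing and linkage, and its difference may be small: in the illustration it is 10.5% v 12.4%, for which power with 143 per arm is only about 8%. The baseline-positive comparison is randomised but smaller still than the group of all known positives.
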